### Statistical Methods

This trial uses a noninferiority and possibly superiority hypothesis testing framework between groups for primary, secondary, and exploratory outcomes. We will report the results in accordance with the noninferiority trials extension of the CONSORT (Consolidated Standards of Reporting Trials) 2010 statement. Tests for noninferiority will be one-sided and performed using a 2.5% significance level. All other tests will be two-sided, performed using a 5% significance level. The type I error rate will be controlled using a hierarchical testing procedure for secondary end points. A subsequent end point will only be tested if the previous end point’s test for noninferiority is statistically significant.

### Criteria Analysis

According to CONSORT 2010, interpreting a noninferiority trial’s results depends on where the CI for the treatment effect lies relative to the margin of noninferiority –∆NI and the null effect. The lower bound of the one-sided (1–α)×100% CI for the treatment effect must be above the margin –ΔNI to declare that noninferiority has been shown [45].

Once noninferiority is evident, it is acceptable to assess whether the new follow-up appears superior to the reference follow-up, using an appropriate test or CI, with a significance level defined a priori and with an intention-to-treat (ITT) and a per-protocol (PP) analysis. All randomized patients will be included in the ITT analysis, including children assessed at T1 or T2, after the time allowed by the protocol. The PP population will include only participants without major deviations. These patients must have completed at least 50% of the prescribed training time and at least 50% of the reading therapy sessions outlined in the protocol.

In this context, if the noninferiority is shown (based on both ITT and PP analyses), superiority will then be tested for the same primary end point, as described in the European Medicines Agency (EMA) guidelines [46]. Superiority will be tested using a *t* test at a 2-sided 5% significance level.

The type I error rate will be controlled using a hierarchical testing procedure for secondary end points. A subsequent end point will only be tested if the previous end point’s noninferiority test is statistically significant.

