Patients assigned to the experimental arm will undergo 12 weeks of reading therapy, with one session every two weeks. In addition, they will use the medical device Poppins Clinical for 20 minutes per day, 5 days a week, over 12 weeks. The Poppins Clinical device is provided free of charge to families during the three-month training period. Each family must create an account in the game using a specially generated link designed to track study participants. The patient’s playtime is recorded by Poppins Clinical—the time spent on each exercise is tracked, enabling the app to monitor the children’s daily playtime. The patient will receive a notification on their tablet every Monday encouraging them to play, and another on Saturday to motivate them to reach the playtime goal. If they have not played during the week, the child will receive an additional notification the following Wednesday to encourage them to play. The first day of training in the Poppins Clinical group must be performed within 2 weeks after the baseline evaluation (T1). Patients in the control arm will continue to receive a weekly reading therapy session, as per common practice in France [15]. To control for potential bias related to the formation of speech and reading therapists, years of graduation and the training courses followed in the last 5 years will be recorded.

A second evaluation (T2) will take place via videoconference 12 weeks (+ or - 14 days) after the first day of training with Poppins Clinical for the experimental arm, or 12 weeks after the baseline evaluation for the control arm. Questionnaires for patients, their legal guardians, and speech and reading therapists will be collected at this time. Please refer to Figure 1 for a flowchart of the study procedures.

Throughout the trial, investigators and evaluators will remain blinded to the patients’ group assignments. However, patients and their speech and reading therapists will not be blinded to the allocation. To maintain blinding of the investigators and evaluators, the CRO’s safety department will be responsible for recording all adverse events and device deficiencies.

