The noninferiority margin represents the maximum clinically acceptable difference between the new treatment and the active control that still allows concluding noninferiority. This margin should be based on a clinical basis, but methods for defining the noninferiority margin can vary widely [47]. The methods used to define the noninferiority margin are frequently not detailed in noninferiority trials, although the choice of the noninferiority margin may strongly impact the conclusion regarding noninferiority trials [47]. Currently, there is no consensus about the best method for defining the noninferiority margin. Previous trials and historical data should be considered if available, however, such data do not always exist. To our knowledge, there is no previous trial or historical evidence regarding the margin that could be clinically relevant in SLD therapy. In that case, the choice of the margin is often based on experts’ opinions [29,47]. The clinically significant margin was determined through consultation with an independent expert committee. A threshold of –5 correctly read words was established as the noninferiority margin based on clinical data and expertise. This decision was based on data from a previous double-blind randomized controlled trial showing a natural progression of 7.7 (SD 12.7) correctly read words over 8 weeks [26] and was unanimously approved by a committee of experts combining clinical experience in learning disabilities with methodological expertise.

The choice of population and how to handle missing data may also affect trial results. ITT analyses may favor noninferiority results, while protocol violations may dilute potential differences between the treatment arms, favoring noninferiority results. Therefore, it is preferable to analyze noninferiority trials using both the ITT and PP approach [48]. We will conduct statistical analysis using both the ITT and PP populations. The PP population includes only participants who have completed at least 50% of the training time prescribed by the protocol. To ensure consistency in reading therapy care within the PP population, each participant must complete at least 50% of the reading therapy sessions outlined in the protocol.

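### The common 50% session floor lets a control child with 6 of about 12 sessions, the experimental arm's full schedule, meet the per-protocol session rule, which weakens the per-protocol set as a guard against dilution

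*Protocol article*

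**What the plan says.** Study Procedure sets the two therapy schedules. The experimental arm has "12 weeks of reading therapy, with one session every two weeks", which is 6 sessions, plus the game. For the control arm, "Patients in the control arm will continue to receive a weekly reading therapy session", with the second evaluation at "12 weeks after the baseline evaluation for the control arm". That makes about 12 sessions; the article gives no count, so the 12 is derived.

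Criteria Analysis defines the PP set: "The PP population will include only participants without major deviations". It then requires at least half of the prescribed training time and "at least 50% of the reading therapy sessions outlined in the protocol". Principal Findings repeats the session rule for everyone: "To ensure consistency in reading therapy care within the PP population, each participant must complete at least 50% of the reading therapy sessions".

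Principal Findings also says why a PP analysis is planned. Departures from protocol can dilute a difference between arms and so make noninferiority easier to show. Criteria Analysis requires noninferiority in both the intention-to-treat (ITT) and the PP analysis before superiority is tested.

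**The concern.** The trial asks whether the game can stand in for half of the therapy sessions. A control child who attends only half of the weekly sessions has lost the part of the comparison that could make the experimental arm look worse. For that child the comparison becomes the game plus 6 sessions against 6 sessions alone. This is easier for the experimental arm than the stated question.

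A percentage floor that is the same in both arms looks even-handed. But one schedule is twice the other, so half of the longer schedule equals all of the shorter one. The floor therefore sits exactly where the session contrast disappears. ITT offers no independent protection, because it contains the same under-attending controls. Noninferiority to weekly therapy could then be supported partly by controls who did not receive weekly therapy.

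**Working it through.** **The plan's own figure.** Inputs from Statistical Justification of the Sample Size: margin 5 words, SD 12.7, one-sided 2.5%, power 90%. The normal approximation is n = 2 × (12.7/5)² × (1.960 + 1.282)² = 135.6, so 136 per group. The noncentral t with d = 5/12.7 = 0.394 gives 137, the figure stated. With 10% dropout, 137/0.9 = 152.2, so 153 per arm and 306 in total. The design figures reproduce and are used below.

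**Session floors.**

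| Arm | Scheduled | 50% floor |
|---|---|---|
| Control | 12 × 1 = 12 | 6 |
| Experimental | 12 / 2 = 6 | 3 |

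If the 14-day window for the second evaluation also applies to controls, 10 to 14 weekly sessions are scheduled and the floor is 5 to 7. The overlap remains.

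**Decision rule.** SE = 12.7 × √(2/137) = 1.534. Noninferiority needs an estimate above −5 + 1.96 × 1.534 = −1.99.

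**Illustration of dilution.** These assumptions are not in the article:
- the true loss is exactly 5 words at full schedules;
- the effect is linear in sessions, with no separate effect of the game, so difference = −(5/6) × (control sessions − experimental sessions);
- there are 137 children per arm in the PP set;
- the rate is for the PP analysis alone.

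Rate = 1 − Φ((−1.99 − difference)/1.534).

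| PP attendance | Mean sessions, control v experimental | Difference | False noninferiority rate |
|---|---|---|---|
| Full in both arms | 12 v 6 | −5.00 | 2.5% |
| 20% at the floor, both arms | 10.8 v 5.4 | −4.50 | 5.1% |
| 20% at the floor, controls only | 10.8 v 6 | −4.00 | 9.5% |
| 75% average, both arms | 9 v 4.5 | −3.75 | 12.6% |
| 75% average, controls only | 9 v 6 | −2.50 | 37.0% |

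The means in the 20% rows are 0.8 × 12 + 0.2 × 6 = 10.8 and 0.8 × 6 + 0.2 × 3 = 5.4.

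**Effect of a higher floor.** With a common 75% floor (9 of 12; 75% of 6 is 4.5, so 5 of 6), the case with 20% at the floor gives:
- both arms: 0.8 × 12 + 0.2 × 9 = 11.4 and 0.8 × 6 + 0.2 × 5 = 5.8, difference −4.67, rate 4.1% instead of 5.1%;
- controls only: 11.4 v 6, difference −4.50, rate 5.1% instead of 9.5%.

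A higher floor limits the dilution but does not remove it.

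**The case against.** **The floor is necessary, not sufficient.** The PP set must first be free of major deviations, and the full protocol may count a control child seen at half frequency as one. This stands as a limit: the article does not prove that every such child is admitted. It does not remove the point. The article gives no tighter session limit, and Principal Findings describes the PP set by the 50% floors alone.

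**The arms are not made alike.** A reader might infer that a control child with 6 sessions erases the whole comparison. The article does not support that. The experimental child is also prescribed the game for 20 minutes, 5 days a week, for 12 weeks. Only the session-frequency part of the contrast is lost.

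**Both arms can miss sessions.** An equal percentage floor keeps the 2:1 ratio when attendance falls alike in both arms. This stands, and it cuts the inflation: 5.1% rather than 9.5%, and 12.6% rather than 37%. It does not bring the rate back to 2.5%, because the absolute gap in sessions still shrinks.

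**The model is simple and covers PP alone.** Both analyses must succeed, so the PP rates are upper bounds on the joint rate. The absence of a game effect is assumed. If the game adds benefit and the net loss is still 5 words, the effect per session must be larger, and each missed control session dilutes more. Controls enter already attending weekly, so an average of 75% may be pessimistic.

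**Unequal floors have a cost.** Selecting the arms by different adherence rules could enrich the control set for more adherent families. This stands and shapes the fix.

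**Conclusion.** The point holds in limited form. On the stated schedules, the PP session floor for controls coincides with the experimental arm's full schedule, and this works against the purpose the article gives for the PP analysis. The overlap follows from the text; the harm is conditional. Under the assumptions listed, the PP false noninferiority rate rises from 2.5% to about 5% (both arms) or 9.5% (controls only) when 20% sit at the floor. At 75% average attendance it is about 13% or 37%.

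A reader might take 37% as the trial's error rate. The documents do not support that: it needs poor attendance among controls only, it ignores the ITT requirement, and the article gives no attendance data. If nearly all controls attend nearly every session, the effect is small. The change is worth making because it is cheap and improves the safeguard, not because the trial is shown to be invalid.

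**What to change.** Before database lock, amend the PP definition in Criteria Analysis and its repeat in Principal Findings so that a PP control child must have attended clearly more than 6 sessions.

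- **Preferred:** one higher percentage in both arms, for example 75% (at least 9 of 12 and 5 of 6). The same adherence rule then selects both arms. The 75% is an example; the article gives no basis for a particular cut.
- **Alternative:** arm-specific floors, with the present 50% rule kept as a sensitivity analysis, because unequal floors can select the arms differently by adherence.
- **Either way:** report sessions attended by arm beside the PP result, and state how major deviations treat controls with low attendance.

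This changes only an analysis set, not the care given or the planned sample size. The cost is a smaller PP set. If 15% of 137 controls fall out, 116 remain and the SE is 12.7 × √(1/137 + 1/116) = 1.60 instead of 1.53. If both arms lose as many, it is 12.7 × √(2/116) = 1.67.

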### Safety Criterion Analysis

The safety population includes all participants who will use the DM Poppins device at least once. This safety population will be used for the safety analysis. Adverse events will be reported by the participant’s parents to the CRO’s Safety Department or the patient coordinator and will be recorded in the eCRF form. The form will contain all necessary variables to define the date, severity, and relationship to the study device, as evaluated by the investigator (see Textbox 1).

Summary of descriptive statistics of adverse events and device deficiencies.

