## Methods

### Study Design and Objectives

This study is an interventional, multicenter, noninferiority randomized trial with two arms. The main objective is to evaluate the noninferiority of Poppins Clinical combined with one reading therapy session every 2 weeks (experimental arm) compared with one reading therapy session every week (control arm) on the reading accuracy (the primary end point) of children with SLD and reading impairment.

Secondary objectives include comparing the experimental group to the control group in terms of safety, reading speed, reading skills, phonological awareness, parental stress, parent quality of life, and text comprehension (secondary end points). Costs related to medical care and therapy between the experimental and control groups are also investigated. This protocol follows SPIRIT (Standard Protocol Items: Recommendations for Interventional Trials) guidelines (checklist provided in Multimedia Appendix 1).

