### Outcomes

The primary outcome of this study is reading accuracy, which will be measured by the number of correctly read words using the EVALEO (Ortho Edition) [37] 2-minute word reading test (EVAL2M). Noninferiority will be evaluated 12 weeks after the start of training with Poppins Clinical for the experimental group or 12 weeks after the baseline evaluation for the control group.

Safety will be assessed by monitoring adverse events reported by patients during the 12-week study duration.

Seven secondary outcomes will also be investigated. Noninferiority in reading speed, measured by the number of words read using the EVAL2M [37], will also be evaluated. In addition, noninferiority in word reading skills (speed and accuracy) and meta-phonological skills will be assessed using respectively the Alouette-R [38] text reading test and the BALE Phoneme Suppression Test [39].

The impact of Poppins Clinical on parents’ stress levels and quality of life will be measured using the Parenting Stress Index-Short Form (PSI-SF) and the EQ-5D-5L [40] quality of life questionnaire. Text comprehension will also be assessed through the computerized BMT-i test battery [41], evaluating correct answers to comprehension questions, as well as reading precision and speed. A cost evaluation will be conducted by administering a questionnaire to parents to evaluate the health and economic value of Poppins Clinical. The objective is to determine in each group the direct and indirect health care costs, including, treatment costs (eg, number of appointments and costs of each session) and work-related costs (eg, the number of days off used for health purposes).

A total of 5 exploratory end points will be investigated. The effect of Poppins Clinical on visual attention span will be assessed with the EVALEO test, using correct answer scores. The patient’s quality of life and reading and writing difficulties will be evaluated using the PedsQL 4.0 CORE [42] young child report and a self-assessment grid for reading and writing difficulties [43]. The perceptions of parents and speech therapists regarding the study’s impact on therapy will be captured via an adapted questionnaire. Finally, predictive factors of training effectiveness with Poppins Clinical will be explored to improve the individualization of the program and the use of the device through connection data.

All the outcomes are described in Table 1.

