All outcomes will be evaluated 12 weeks after the start of training for the experimental group or 12 weeks after the baseline evaluation for the control group. Participants of the experimental group will have up to 14 calendar days to start training with Poppins Clinical once the baseline evaluation is completed. The results will be entered into an electronic case report form (eCRF) hosted on the web by the CRO, which will be responsible for data monitoring and treatment.

**Table 1 table1:** Measured outcomes investigated in the protocol.

Outcome	Measure
Primary outcome	Reading accuracy is measured by the number of correctly read words (EVAL2M)
Safety secondary outcome	Number of adverse events reported during the study
Secondary outcome 1	Reading speed is measured by the number of read words (EVAL2M)
Secondary outcome 2	Word reading accuracy and speed (Alouette-R)
Secondary outcome 3	Cost evaluation
Secondary outcome 4	Phoneme suppression skills (BALE)
Secondary outcome 5	Parental stress levels measured using the Parenting Stress Index Short Form
Secondary outcome 6	Parent’s quality of life measured using the EQ-5D-5L
Secondary outcome 7	Reading precision, speed, and comprehension (BMT-i)
Exploratory outcome 1	Visual attention span (EVALEO)
Exploratory outcome 2	Child’s quality of life (PedsQL 4.0 CORE)
Exploratory outcome 3	Child’s perception of reading and writing difficulties [43]
Exploratory outcome 4	Perception of parents and speech therapists on the impact of the protocol on the child (custom questionnaire)
Exploratory outcome 5	Evaluation of predictive factors of training effectiveness

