**For adverse events:**
Type of adverse eventSeverityEvolutionRelationship with the deviceNumber of episodesTime of onset of the adverse event (defined as the time from first use to the earliest date of the adverse event)Number of participants with at least one episode (and percentage)Discontinuations will also be summarized.

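### The only defined safety population is device users, so the stated experimental-versus-control safety comparison has no control children in it

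*Protocol article*

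**What the plan says.** The Study Design and Objectives section sets a between-arm aim: "Secondary objectives include comparing the experimental group to the control group in terms of safety". The Outcomes section places no arm restriction on the monitoring: "Safety will be assessed by monitoring adverse events reported by patients during the 12-week study duration". Table 1 gives the safety secondary outcome as "Number of adverse events reported during the study".

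The Safety Criterion Analysis section then fixes the analysis set: "The safety population includes all participants who will use the DM Poppins device at least once". It adds: "This safety population will be used for the safety analysis". The article names no other set for safety. The accompanying textbox measures onset of an event in a way that fits device users, "defined as the time from first use to the earliest date of the adverse event", and also lists relationship with the device and device deficiencies.

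Under Study Procedure, the experimental children have fortnightly therapy sessions and, in addition, "they will use the medical device Poppins Clinical for 20 minutes per day, 5 days a week, over 12 weeks". For the others, "Patients in the control arm will continue to receive a weekly reading therapy session, as per common practice in France". Under Study Population, anyone who has used this game or its predecessor is excluded.

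**The concern.** The objective needs an adverse event denominator in each arm. The analysis set supplies one only for children who have opened the game, and no child assigned to control is meant to do so. Both rules are stated, so an analysis plan that follows one must depart from the other. This is not detail left to a fuller document.

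The tested strategy is the game together with fewer therapy sessions. An experimental child who never opens the game is still assigned the reduced sessions but drops out of the safety set. The Discussion foresees that home training might provoke behavioral problems such as refusal to use the device. Such events also occur without any intervention in children aged 7 to 11, and parents, who report the events, know the allocation. Without a concurrent control rate, the safety summary is an uncontrolled count that cannot be set against background events.

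**Working it through.** **1. Denominators.** The plan's own numbers reproduce. With a margin of 5 words and an SD of 12.7, the standardized difference is 5 / 12.7 = 0.394. A two-sample *t* test at one-sided 2.5% with 137 per arm has power 0.901 (the normal approximation gives 136 per arm for 90%). Allowing for 10% drop-out, 137 / 0.90 = 152.2, rounded up to 153 per arm and 306 in total. These figures serve here only as arm sizes. The article gives no figure for the safety analysis.

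**2. Applying the set definition to the arms.** Let k be the number of experimental children who never start the game. The article does not give k.

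| Arm | Randomized | In the safety set as written |
|---|---|---|
| Experimental | 153 | 153 − k |
| Control | 153 | 0, as assigned |
| Total | 306 | 153 − k |

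The number left out is 153 + k, at least 153 / 306 = 50% of those randomized. Earlier use cannot bring a control child in, because it is an exclusion criterion. The one remaining route is a control child who obtains the game during the trial. That is contamination and gives no valid comparator.

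**3. Setting the set against the objective.** Any comparison of event percentages, even a purely descriptive one, needs p(experimental) and p(control). With a control denominator of 0, p(control) does not exist, so no difference can be estimated. Time from first use is likewise undefined for controls and for non-starters.

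**4. What a set of all randomized children would give.** The article states no event rate, so a range is assumed. With the same proportion p in both arms and 153 per arm, the half-width of the 95% CI for the difference is 1.96 × √(2p(1 − p) / 153):

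- p = 5%: ±4.9 percentage points
- p = 10%: ±6.7 percentage points
- p = 20%: ±9.0 percentage points

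**5. Observation window.** On nominal dates, the control T2 falls 12 weeks (84 days) after T1. The experimental T2 falls 12 weeks after the first training day, which may be up to 14 days after T1, so up to 84 + 14 = 98 days after T1. The ratio is 98 / 84 = 1.17, that is, up to 17% more time in which an event can be recorded. This leaves aside the visit tolerance around T2. A raw T1-to-T2 count would therefore tilt against the experimental arm.

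**The case against.** The strongest reply is that safety here is a device matter and is described, not tested. The comparative aim rests on one sentence in a list. Safety stands apart from the seven numbered secondary outcomes, the textbox promises descriptive statistics, and its items are largely device-oriented. A device-exposed set suits those items, and counting onset from first use is sensible within it, so that definition is not a second error. This much stands, and it is why the device-user subset should be kept. It does not rescue the stated aim, because a descriptive comparison also needs controls.

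Two stronger inferences are tempting, and the article supports neither.

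- A reader might infer that control-arm events are not collected. The Outcomes section monitors events over the 12-week study without naming an arm, the CRO's safety department is to record every adverse event, and parents report without distinction of arm. The fault shown is in the analysis set, not in data capture.
- A reader might infer that the trial is blind to harm from fewer sessions in non-starters. The most direct such harm is poorer reading. That is the primary outcome, and the intention-to-treat analysis includes every randomized child. Parental stress and the quality of life of parent and child are also measured. What the safety set loses is adverse events as such in these children.

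**Conclusion.** The point holds as an internal contradiction. The stated between-arm safety objective cannot be met from the only safety set that the article defines, which as assigned contains at most 153 experimental and 0 of 153 control children and leaves out experimental non-starters. This rests on the planned 1:1 allocation of 306 and on controls not obtaining the game.

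The consequence is confined to the safety comparison. The margin, sample size, primary analysis and hierarchical testing are unaffected. With no expected event rate and no expected number of non-starters in the article, the effect on any safety conclusion cannot be quantified beyond set membership. It should be corrected before the safety analysis is run, because a stated objective depends on it.

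**What to change.** Make the Study Design and Objectives section, the Safety Criterion Analysis section and its textbox agree.

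- **Comparative set.** Define it as all randomized children, summarized by randomized arm, with any control child who used the game flagged. Grouping by care actually received would leave experimental non-starters (fewer sessions, no game) in no clear group.
- **Collection.** Confirm that adverse events are solicited in the same way in both arms.
- **Summary.** Report the number and percentage of children with at least one event by arm, with a 95% CI for the difference, over a common window starting at randomization or T1. Alternatively, report events per person-time, given the possible 14-day difference in follow-up.
- **Device-user subset.** Keep it for device deficiencies, relationship with the device and time from first use.
- **Alternative.** If only a description of device users is intended, reword the objective so that it no longer promises a comparison of the arms on safety.

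The cost is mainly wording. The event form already exists, control families are already followed to T2, and the sample size stays at 306. Only if solicitation proves to differ between arms would data collection itself have to change.

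### The investigator is to stay blinded throughout, yet is also assigned to judge whether each adverse event is related to a device that only the experimental arm uses

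*Protocol article*

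**What the plan says.** Two sections of the protocol article bear on this.

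- **Study Procedure** sets the masking: "Throughout the trial, investigators and evaluators will remain blinded to the patients’ group assignments". It adds that "patients and their speech and reading therapists will not be blinded to the allocation". To preserve the blind it removes one task from the sites: "the CRO’s safety department will be responsible for recording all adverse events and device deficiencies".
- **Safety Criterion Analysis** sets out how events are collected and analysed. Parents report to the CRO's safety department "or the patient coordinator and will be recorded in the eCRF form". On content it says: "The form will contain all necessary variables to define the date, severity, and relationship to the study device, as evaluated by the investigator". On who is analysed it says: "The safety population includes all participants who will use the DM Poppins device at least once". The textbox in the same section lists relationship with the device among the adverse-event summaries and counts time of onset from first use.

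The control arm continues weekly reading therapy and receives no device. The limitations paragraph of the Discussion confirms that no placebo is used. The title calls the trial investigator-blinded, and the Conclusion calls it single-blind.

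**The concern.** The authors evidently saw that adverse-event information can reveal the arm, since they moved its recording away from the investigators for that stated reason. The safety section then gives the investigator the part of the adverse-event work most closely tied to allocation, namely whether the device caused the event. Both sections use the same role name, and the article names no separate, unblinded investigator for the task.

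Two things are at stake. The first is the masking itself: children, families and therapists know the allocation, so investigator and evaluator blinding is all the masking the trial has. The second is the safety result. Relationship to the device is a planned summary for a medical device, and a rating made without knowledge of exposure says little about causality.

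**Working it through.** No figure in the article bears on this point, so the check sets the statements side by side and follows each through.

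1. **Who is blinded, and for how long.** Study Procedure: "investigators and evaluators will remain blinded", for the whole trial. A causality rating made after T2 but before the trial ends would still fall inside that period.
2. **What is moved to protect the blind.** Study Procedure: the CRO's "safety department will be responsible for recording all adverse events and device deficiencies". This covers recording only.
3. **Who judges device relationship.** Safety Criterion Analysis: the investigator.
4. **Who has a device.** By design, experimental-arm children only. For any child, knowing that the device was used is the same as knowing the arm.
5. **Whose events are analysed.** Those of children who used the device at least once, which by design means the experimental arm. Onset time counted from first use is likewise defined only for these children.

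The article does not say which events reach the investigator or what they contain. The possible cases are these:

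| What the investigator receives | Blind | Causality rating |
|---|---|---|
| Events of device users only | Lost: receiving the event reveals the arm | Informed by exposure |
| Events from both arms, with exposure shown or recognisable from the description | Lost for those children | Informed by exposure |
| Events from both arms, with exposure removed | Kept | Made without knowing exposure; control-arm ratings fall outside the safety population |

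In the first two cases the Study Procedure statement fails. In the third it holds, but the planned summary of relationship with the device loses most of its meaning. In a trial with a sham, a blinded investigator can rate relationship to the study product because every child received something that could be that product. That does not apply here.

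The reports also start with unblinded parents, so a description may mention the game even when no arm code is displayed.

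**The case against.** The strongest reply is that recording and evaluating are different acts. Study Procedure moves the first and Safety Criterion Analysis assigns the second, so the wording is not contradictory on its face. An investigator could rate a redacted narrative, conditional on exposure, for events in either arm. The safety population and the onset variable define the analysis and do not prove that only device users' events are sent to the investigator. Redaction rules, eCRF access rights and delegation of the causality task normally sit in a full protocol or safety plan, which is not shown.

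Much of this stands. The absence of those operational details is not a fault in a journal article, and it would be too strong to say that no procedure could satisfy both sections. What remains is that the one procedure that keeps the blind does so by withholding the fact a causality judgement needs. The article also positively names the investigator as the person who rates device relationship, so this is a conflict in what is stated, not an omission.

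A reader might infer three further things that the documents do not support:

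- **That EVAL2M scoring is biased.** Study Procedure lists investigators and evaluators separately. The investigator checks eligibility, while a speech therapist from the clinical site carries out the baseline evaluation. Nothing says that the investigator scores EVAL2M or tells the evaluator the arm.
- **That game malfunctions reach the investigator.** The investigator's evaluation is tied to the adverse-event form. For device deficiencies the textbox lists only type and duration, and no text sends them to the investigator.
- **That 153 children are affected.** This is the planned size of the experimental arm. It would be the number affected only if every child in it had a reported event.

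**Conclusion.** The point holds as an inconsistency between Study Procedure and Safety Criterion Analysis that should be resolved. As written, the investigator either learns the arm of children with adverse events or rates device causality blind to exposure. The shown harm is to the investigator-blinded claim and to the interpretation of the causality summary. An effect on the primary outcome is possible if the arm passes from investigator to evaluator within a site, but it is not shown. With no event rate in the article, its size cannot be estimated.

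This rests on two assumptions: that the investigator named in the safety section is the one kept blinded in Study Procedure, since the article distinguishes no other, and that control-arm children do not use the device during the trial.

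**What to change.** Reconcile the two sections as follows:

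- **Assessor.** In Safety Criterion Analysis, replace the investigator with a named, medically qualified, unblinded assessor who is neither a blinded investigator nor an evaluator. The CRO's safety function is a natural place, assuming that it has such a person; the article mentions only a department that records and receives events. Any other qualified person outside the blinded roles would serve equally well.
- **Access.** State in Study Procedure that site investigators and evaluators cannot open the adverse-event pages of the eCRF until that child's T2 has been scored. If the full protocol already provides for this, a short reference is enough.
- **Unblinding.** Log each case in which a site investigator has to learn the allocation, with its date relative to T2, so that the integrity of the blind can be reported.

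The cost is a small reassignment of the causality task, a change to eCRF access rights, a few sentences of text and case-by-case logging. It is higher if the CRO's safety function lacks a qualified assessor and one has to be appointed. Sample size, endpoints and visit schedule are unaffected.
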